**Communication**

| I can | Never tried_1_ | Not at all_2_ | Not very easily_3_ | Somewhat easily_4_ | Very easily_5_ |
| --- | --- | --- | --- | --- | --- |
| Open emails |  |  |  |  |  |
| Send emails |  |  |  |  |  |

**Internet**

| I can | Never tried_1_ | Not at all_2_ | Not very easily_3_ | Somewhat easily_4_ | Very easily_5_ |
| --- | --- | --- | --- | --- | --- |
| Find information about local community resources on the Internet |  |  |  |  |  |
| Find information about my hobbies and interests on the Internet |  |  |  |  |  |

**Calendar**

| I can | Never tried_1_ | Not at all_2_ | Not very easily_3_ | Somewhat easily_4_ | Very easily_5_ |
| --- | --- | --- | --- | --- | --- |
| Use a computer/smartphone/tablet to enter events and appointments into a calendar |  |  |  |  |  |
| Check the date and time of upcoming and prior appointments |  |  |  |  |  |

**Entertainment**

| I can | Never tried_1_ | Not at all_2_ | Not very easily_3_ | Somewhat easily_4_ | Very easily_5_ |
| --- | --- | --- | --- | --- | --- |
| Use a computer/smartphone/tablet to watch movies and videos |  |  |  |  |  |
| Use a computer/smartphone/tablet to listen to music |  |  |  |  |  |

**General Health Status**

We would like to know how good or bad your health is TODAY. The scale is numbered from 0 to 100. 100 means the best health you can imagine. 0 means the worst health you can imagine. Mark an X on the scale to indicate how your health is TODAY. Now, please write the number you marked on the scale in the box below.

Your health today =

[figure not shown]

**Diabetes Related Health Status**

1. We would like to know your height. Would you like to answer in imperial (feet, inches) or metric (metres, centimetres) units? Please specify date DD/MM/YYYY.

□ Imperial (feet, inches)

□ Metric (metres, centimetres)

[Based on answer skip to drop down menus to select height in preferred units]

1. **How was this height measured:** (if other please specify)

□ Myself

□ Doctor

□ Other, please specify_________________________

□ Don’t know

□ Prefer not to say

1. We would like to know your weight. Would you like to answer in imperial (stones, pounds) or metric (kilograms) units? Please specify date DD/MM/YYYY.

□ Imperial (stones and pounds)

□ Metric (kilograms)

[Based on answer skip to drop down menus to select weight in preferred units]

1. **How was this weight measured:** (if other please specify)

□ Myself

□ Doctor

□ Other, please specify_________________________

□ Don’t know

□ Prefer not to say

1. We would like to know your waist size. Would you prefer to answer in imperial (inches) or metric units (centimetres)? Please specify date DD/MM/YYYY.

□ Imperial (inches)

□ Metric (centimetres)

[Based on answer skip to drop down menus to select waist size in preferred units]

[figure not shown]
Above the belly button, just below the rib cage. Bend to one side to find natural crease of your waist. Measure across at this point.

1. **How was this waist size measured:** (if other please specify)

□ Myself

□ Doctor

□ Other, please specify_________________________

□ Don’t know

□ Prefer not to say

1. What is your most recent blood glucose (sugar) level? (HbA1c mmol/mol)

□ Don’t know

□ Prefer not to say

1. What is the date of your most recent blood glucose level measurement?

DD/MM/YYYY

□ Don’t know

□ Prefer not to say

1. What is your most recent blood pressure level?

Systolic (top number) mmHg [drop down menu – 70, 80, 90, 100, 110, 120, 130, 140, 150, 160, 170, 180, 190]

Diastolic (bottom number) mmHg [drop down menu – 40, 50, 60, 70, 80, 90, 100]

□ Don’t know

□ Prefer not to say

1. What was the date of your most recent blood pressure level?

DD/MM/YY

□ Don’t know

□ Prefer not to say

1. What was your most recent HDL cholesterol level (mmol/L)?

[drop down menu]

□ Don’t know

□ Prefer not to say

1. What was your most recent TOTAL cholesterol level?

______________ mmol/L [drop down menu]

□ Don’t know

□ Prefer not to say

1. What is the date of your most recent cholesterol measurement?

DD/MM/YYYY

□ Don’t know

□ Prefer not to say

1. Do you smoke?

□ Yes

□ No

**Confidence regarding diabetes management and meal planning**

1. How confident do you currently feel in managing your diabetes?

| 1 – Very unconfident | 2 | 3 | 4 | 5 – Neither confident nor unconfident | 6 | 7 | 8 | 9 | 10 – Very confident |
| --- | --- | --- | --- | --- | --- | --- | --- | --- | --- |
|  |  |  |  |  |  |  |  |  |  |

1. How confident do you currently feel in making healthy food choices?

| 1 – Very unconfident | 2 | 3 | 4 | 5 – Neither confident nor unconfident | 6 | 7 | 8 | 9 | 10 – Very confident |
| --- | --- | --- | --- | --- | --- | --- | --- | --- | --- |
|  |  |  |  |  |  |  |  |  |  |

1. How confident do you currently feel in planning meals efficiently?

| 1 – Very unconfident | 2 | 3 | 4 | 5 – Neither confident nor unconfident | 6 | 7 | 8 | 9 | 10 – Very confident |
| --- | --- | --- | --- | --- | --- | --- | --- | --- | --- |
|  |  |  |  |  |  |  |  |  |  |

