3.2 Primary endpoint/outcome

The primary outcomes are categorized as follows: (1) Outcomes directly related to the health status and condition management of the participants (e.g. weight, BMI, HbA1c, blood pressure, waist, generic health status, smoking yes/no, confidence in diabetes management and meal planning, healthy eating) and (2) Outcomes directly related to platform intervention usage:

- Number / Duration of sessions
- Number of users / average sessions per user
- New users
- Monthly Active Users / Weekly Active Users
- Specific actions:
  - # Recipes Viewed, (any indication on favourite content)
  - # Recipe Added / Saved
  - # Meal Plans created
  - # Shopping Actions
    - Carts sent online
    - Meal plans sent to cart
    - In store shopping actions - print, email, sms, app, etc.
    - Number of items shopped / value
- Platform used - app vs web app
- GA audience metrics: Demographics, Geography,
- User Retention
- Top 20 recipes (potentially)
- The average or typical meal plan including health score (potentially)

Additionally, expectations beforehand and satisfaction afterwards will be assessed. Diabetes UK will collect data regarding their traffic on the website and the amount of referrals to the online platform.

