**6.1 Inclusion criteria**

Project participants:

- Diagnosis Type 1
- Diagnosis Type 2 or at risk for Diabetes Type 2
- Relatives taking care of people with Type 1 or Type 2 Diabetes (or at risk)
- Good understanding of written and spoken English language

Platform development staff: Good understanding and know-how of platform and current project

Diabetes UK staff: Qualified and experienced dieticians working with people having Type 1 Diabetes, Type 2 Diabetes or those who are at risk for developing Type 2 Diabetes.

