**Expectations**

1. I think that the platform will help me to manage my diabetes

| 1 – Very Strongly disagree | 2 | 3 | 4 | 5 – Neither agree nor disagree | 6 | 7 | 8 | 9 | 10 – Very strongly agree |
| --- | --- | --- | --- | --- | --- | --- | --- | --- | --- |
|  |  |  |  |  |  |  |  |  |  |

Please explain your rating _________________________

1. The platform will help me to make healthy food choices

| 1 – Very Strongly disagree | 2 | 3 | 4 | 5 – Neither agree nor disagree | 6 | 7 | 8 | 9 | 10 – Very strongly agree |
| --- | --- | --- | --- | --- | --- | --- | --- | --- | --- |
|  |  |  |  |  |  |  |  |  |  |

Please explain your rating _________________________

1. The platform will help me to plan my meals more efficiently

| 1 – Very Strongly disagree | 2 | 3 | 4 | 5 – Neither agree nor disagree | 6 | 7 | 8 | 9 | 10 – Very strongly agree |
| --- | --- | --- | --- | --- | --- | --- | --- | --- | --- |
|  |  |  |  |  |  |  |  |  |  |

Please explain your rating _________________________

1. Using the platform will improve my food shopping experience

| 1 – Very Strongly disagree | 2 | 3 | 4 | 5 – Neither agree nor disagree | 6 | 7 | 8 | 9 | 10 – Very strongly agree |
| --- | --- | --- | --- | --- | --- | --- | --- | --- | --- |
|  |  |  |  |  |  |  |  |  |  |

Please explain your rating _________________________

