**Confidence regarding diabetes management and meal planning**

1. The platform made me feel more confident in managing my diabetes

| 1 – Very strongly disagree | 2 | 3 | 4 | 5 – Neither agree nor disagree | 6 | 7 | 8 | 9 | 10 – Very strongly agree |
| --- | --- | --- | --- | --- | --- | --- | --- | --- | --- |
|  |  |  |  |  |  |  |  |  |  |

1. After using the platform, I felt more confident in making healthy food choices

| 1 – Very strongly disagree | 2 | 3 | 4 | 5 – Neither agree nor disagree | 6 | 7 | 8 | 9 | 10 – Very strongly agree |
| --- | --- | --- | --- | --- | --- | --- | --- | --- | --- |
|  |  |  |  |  |  |  |  |  |  |

1. After using the platform, I feel more confident planning meals

| 1 – Very unconfident | 2 | 3 | 4 | 5 – Neither confident nor unconfident | 6 | 7 | 8 | 9 | 10 – Very confident |
| --- | --- | --- | --- | --- | --- | --- | --- | --- | --- |
|  |  |  |  |  |  |  |  |  |  |

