**Satisfaction**

1. The platform supported me in diabetes management

| 1 – Very Strongly disagree | 2 | 3 | 4 | 5 – Neither agree nor disagree | 6 | 7 | 8 | 9 | 10 – Very strongly agree |
| --- | --- | --- | --- | --- | --- | --- | --- | --- | --- |
|  |  |  |  |  |  |  |  |  |  |

Please explain your rating _________________________

1. The platform supported me in making healthy food choices?

| 1 – Very Strongly disagree | 2 | 3 | 4 | 5 – Neither agree nor disagree | 6 | 7 | 8 | 9 | 10 – Very strongly agree |
| --- | --- | --- | --- | --- | --- | --- | --- | --- | --- |
|  |  |  |  |  |  |  |  |  |  |

Please explain your rating _________________________

1. The platform supported me in planning my meals more efficiently and within budget?

| 1 – Very Strongly disagree | 2 | 3 | 4 | 5 – Neither agree nor disagree | 6 | 7 | 8 | 9 | 10 – Very strongly agree |
| --- | --- | --- | --- | --- | --- | --- | --- | --- | --- |
|  |  |  |  |  |  |  |  |  |  |

Please explain your rating _________________________

1. The platform supported me in my food shopping experience?

| 1 – Very Strongly disagree | 2 | 3 | 4 | 5 – Neither agree nor disagree | 6 | 7 | 8 | 9 | 10 – Very strongly agree |
| --- | --- | --- | --- | --- | --- | --- | --- | --- | --- |
|  |  |  |  |  |  |  |  |  |  |

Please explain your rating _________________________

5. Did the platform teach you anything else, apart from what is mentioned above?

□ Yes, please explain your answer _________________________

□ No, please explain your answer _________________________

6. Are there any features of this platform that you particularly liked?

□ Yes, please explain your answer _________________________

□ No, please explain your answer _________________________

7. Are there any features of this platform that you particularly disliked?

□ Yes, please explain your answer _________________________

□ No, please explain your answer _________________________

8. Did you encounter any technical problems?

□ Yes, please explain your answer _________________________

□ No, please explain your answer _________________________

9. The platform is a valuable addition to the Diabetes UK learning environment?

| 1 – Very Strongly disagree | 2 | 3 | 4 | 5 – Neither agree nor disagree | 6 | 7 | 8 | 9 | 10 – Very strongly agree |
| --- | --- | --- | --- | --- | --- | --- | --- | --- | --- |
|  |  |  |  |  |  |  |  |  |  |

Please explain your rating _________________________

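### Confidence in managing diabetes is scored for at-risk respondents who have no diabetes to rate, with no not-applicable answer, no way to identify them, and no record of proxy answers

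*Combined protocol and SAP*

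**What the plan says.** Section 3.2 places "confidence in diabetes management and meal planning, healthy eating" in the first of its two primary outcome categories. Attachment 4 (first survey) measures the diabetes part with "How confident do you currently feel in managing your diabetes". The answer is a number from 1 to 10, labelled at both ends and at "5 – Neither confident nor unconfident". Attachment 6 (second survey) asks for agreement, again from 1 to 10, with "The platform made me feel more confident in managing my diabetes". Neither item offers a not-applicable, don't-know or decline answer.

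The Expectations part of Attachment 4 has "I think that the platform will help me to manage my diabetes", and expectations are a planned moderator in Sections 7.5.1 and 8.4. The Satisfaction part of Attachment 6 has "The platform supported me in diabetes management". Section 3.2 mentions expectations and satisfaction only as additions to the two primary categories.

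Section 6.1 admits "Diagnosis Type 2 or at risk for Diabetes Type 2", and also relatives who care for someone with diabetes or at risk of it. Section 6.2 sets no exclusions. Section 8.5 sets aside people who withdraw and people who do not share usage data, but nobody on grounds of diagnosis. Both surveys open by asking respondents to fill in what they can, for themselves or for the person in their care.

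Section 7.1.1 says the first survey will establish diagnosis, at-risk status included. The relationship question in Attachment 4 offers Type 1, Type 2, gestational, a relative with Type 1, a relative with Type 2, another type (free text) and a decline option. It has no at-risk option.

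**The concern.** A person at risk of Type 2 diabetes has no diabetes to manage, so no number from 1 to 10 answers the confidence item. That person must leave it blank, choose a number that means something else, or rate a different thing. The plan then analyses the result with everyone else's under a primary outcome.

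For a carer the difficulty is different. A proxy answer is allowed, but the item does not settle whether it concerns the carer's confidence or the patient's, and no field records which was given.

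What is at stake is interpretation. A pooled mean would combine a person's confidence in managing their own condition, a carer's rating for someone else, and numbers from people for whom the question has no meaning. A contrast by diagnosis, or a moderator analysis using the expectation item, could partly reflect whether the question applied and not what the platform did.

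**Working it through.** The plan gives no figure to reproduce. Section 8.1 states that the anticipated 200 to 300 surveys were not derived statistically. The check is therefore mainly a reading of the documents, with arithmetic to show what can and cannot be said about size.

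**1. Does the instrument protect the item elsewhere?** The HbA1c, blood pressure and cholesterol questions in both surveys offer don't-know and decline answers. Routing is shown for the choice of measurement units. Neither device is used for the diabetes-management items, so the gap is out of line with the surveys' own style.

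**2. Can the affected answers be removed afterwards?** Relatives can be partly identified from the relationship question. At-risk respondents cannot be reliably identified: they may choose the free-text other type, the decline option, a relative option if they also have such a relative, or nothing. Section 8.6, on missing or spurious data, deals with recording and withdrawal and gives no rule for a blank or inapplicable answer.

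**3. Effect on a pooled mean at one time point.** Let A be the mean among people with diabetes, B the mean among people for whom the item does not apply, and p their share. None of these is in the documents.

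Pooled mean = (1 − p)A + pB, so the shift from A is p(B − A). With A = 7 assumed:

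| p | B = 5 | B = 9 |
|---|---|---|
| 10% | 6.8 (−0.2) | 7.2 (+0.2) |
| 25% | 6.5 (−0.5) | 7.5 (+0.5) |
| 40% | 6.2 (−0.8) | 7.8 (+0.8) |

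The sign depends wholly on B. If these respondents leave the item blank, they do not shift the mean at all.

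**4. Effect on a before/after change.** Suppose, contrary to the surveys, that both items used one scale. With a true mean change of 1.0 among people with diabetes and a share of 20%, the pooled change is 0.8 × 1.0 + 0.2 × m, where m is the mean change among the others:

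- m = −4 gives 0.0
- m = 0 gives 0.8
- m = +4 gives 1.6

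Shrinkage by the factor (1 − p) is only the m = 0 case.

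**5. Is there a common scale?** No. The first survey asks for a current level; the second asks for agreement that the platform raised it. A respondent with no change who picks the neutral 5 at follow-up would show 5 − 3 = +2, 5 − 5 = 0, 5 − 8 = −3 or 5 − 10 = −5, depending only on the baseline answer. No valid change score can be formed from this pair for anyone, with or without diabetes.

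**6. Would excluding these answers cost precision?** Again this supposes a common scale, with a standardised change d = 0.2, two-sided alpha 0.05, n = 200 and a share of 20% (all but n assumed). Power = Φ(d√n − 1.96).

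- Excluded, n = 160: 0.2 × 12.649 − 1.96 = 0.570, power 71.6%.
- Kept, with zero mean change and the same SD: d becomes 0.16/√(1 + 0.2 × 0.8 × 0.2²) = 0.1595; 0.1595 × 14.142 − 1.96 = 0.296, power 61.6%.
- Kept, with the same number ticked both times: power 71.2%.

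In these cases a smaller denominator is not a loss of power. They describe a supposed common scale, not the instruments as written.

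**The case against.** The strongest reply has four parts.

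**Carers are provided for.** The opening instruction in both surveys lets them answer for the person they look after. A reader might infer that relatives cannot be validly scored; the documents do not support that. What remains is an unsettled target and no self/proxy record.

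**Nobody is stated to be forced to answer.** Respondents are asked only to complete what they can, so an at-risk person may leave the item blank. This stands as a possibility. However, a blank could mean inapplicable, unknown or declined, and Section 8.6 does not tell them apart.

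**The analysis could be limited to people who tick Type 1 or Type 2.** It could, and Sections 7.5.4 and 8.3.2 already describe survey results by diagnosis. But the plan states no such restriction for these items, Section 8.4 omits diagnosis from the subgroup list that Section 7.5.1 gives, and the restriction would drop people with gestational or another diabetes, who do have a condition to manage.

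**Not all four items are equally affected.** The satisfaction item does not speak of the respondent's own diabetes, so a carer can answer it directly. The expectation and satisfaction items also invite a free-text explanation, and neither is clearly part of the primary outcome. This is correct: the point rests on the two confidence items and, through the moderator analysis, on the expectation item.

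**Conclusion.** The point stands for the two confidence items and the expectation item. At-risk respondents are eligible and analysed, have no valid answer on the scale, and cannot be reliably separated later. Carers' answers are usable, but it is not recorded whose confidence they describe. The pooled score mixes constructs.

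A reader might go further and infer that these answers pull the result towards neutral or dilute a platform effect. The documents do not support that. They give neither the share of such respondents nor how they would answer; the shift p(B − A) can have either sign; and the proportional shrinkage of a change needs both zero change in this group and a common before/after scale, which the two items do not share. Size and direction are therefore unknown, and every numerical value assumed for A, B, p, m and d above is illustrative.

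The weight is moderate. This is one of many listed outcomes in an exploratory project without formal hypotheses, but it is among the primary ones and the defect is cheap to remove.

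**What to change.** 1. Add an answer such as *Not applicable: neither I nor the person I am answering for has diabetes* to the two confidence items and the expectation item on diabetes management, and to the satisfaction item for consistency. An option that referred only to the respondent would lead carers to opt out, against the surveys' own instruction.
2. Add an at-risk category to the relationship question in Attachment 4, as Section 7.1.1 already presupposes, and a field recording whether answers are the respondent's own or given for someone else.
3. State in Section 8.3.2 that these items are analysed only where there is diagnosed diabetes of any type, including gestational and other types, with proxy answers reported separately. Keep the food-choice and meal-planning items for everyone.
4. Reconcile the subgroup lists in Sections 7.5.1 and 8.4 on diagnosis.

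The cost is one option on four survey items, two small additions to the first survey and a short addition to the analysis text. The denominator for these items falls by an amount the documents do not give. For assumed shares of 10% to 40%, 200 × (1 − p) leaves 180 down to 120, and 300 × (1 − p) leaves 270 down to 180.

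This does not repair the difference in wording and scale between the two confidence items. That is a separate defect and needs its own correction before any before/after change is reported.

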**Healthy eating**

1. Do you eat at least 2 portions (200g) of fruit everyday?

□ Always

□ Often

□ Sometimes

□ Never

1. Do you eat at least 2 portions (200g) of vegetables everyday?

□ Always

□ Often

□ Sometimes

□ Never

1. Your diet:

□ Is different everyday

□ Is different only sometimes during a week

□ Is different only during weekend days

□ Is very monotonous

1. Do you drink at least 1 – 1.5 litre mineral water every day?

□ Always

□ Often

□ Sometimes

□ Never

1. Your snacks are based mainly on:

□ Fruit/fruit juice and milk shakes/yoghurt

□ Biscuits/crackers/bread/stick bread

□ Fried patatos/popcorn/krapfen/peanuts/soft drinks

□ Sweets/chocolate/ice cream/cakes

1. Do you eat breakfast?

□ Always

□ Often

□ Sometimes

□ Never

1. How many times do you eat sweets and cakes in 1 week?

□ 1-2

□ 3-4

□ 1 time a day

□ more than 1 time daily

□ 1 time in 10-15 days

□ never

1. How many times do you eat fish in 1 week?

□ 1-2

□ 3-4

□ 1 time a day

□ more than 1 time daily

□ 1 time in 10-15 days

□ never

**Expectations**

1. I think that the platform will help me to manage my diabetes

| 1 – Very Strongly disagree | 2 | 3 | 4 | 5 – Neither agree nor disagree | 6 | 7 | 8 | 9 | 10 – Very strongly agree |
| --- | --- | --- | --- | --- | --- | --- | --- | --- | --- |
|  |  |  |  |  |  |  |  |  |  |

Please explain your rating _________________________

1. The platform will help me to make healthy food choices

| 1 – Very Strongly disagree | 2 | 3 | 4 | 5 – Neither agree nor disagree | 6 | 7 | 8 | 9 | 10 – Very strongly agree |
| --- | --- | --- | --- | --- | --- | --- | --- | --- | --- |
|  |  |  |  |  |  |  |  |  |  |

Please explain your rating _________________________

1. The platform will help me to plan my meals more efficiently

| 1 – Very Strongly disagree | 2 | 3 | 4 | 5 – Neither agree nor disagree | 6 | 7 | 8 | 9 | 10 – Very strongly agree |
| --- | --- | --- | --- | --- | --- | --- | --- | --- | --- |
|  |  |  |  |  |  |  |  |  |  |

Please explain your rating _________________________

1. Using the platform will improve my food shopping experience

| 1 – Very Strongly disagree | 2 | 3 | 4 | 5 – Neither agree nor disagree | 6 | 7 | 8 | 9 | 10 – Very strongly agree |
| --- | --- | --- | --- | --- | --- | --- | --- | --- | --- |
|  |  |  |  |  |  |  |  |  |  |

Please explain your rating _________________________

**Thank you for filling in the first survey.**

You will be send a link to the second survey (hosted by Qualtrics) in 8 weeks.

